## FLOWCHART OF THIS STUDY

The single-arm, non-randomized clinical trial in second step will consist of selecting patients classified as code green (low risk), who will undergo two medical consultations and two physical examinations (Tytocare® and traditional), with the aim of comparing the results between these two modalities of examination and diagnosis. The flowchart will be as detailed in the steps below and illustrated in figure 1.

[figure not shown]

Figure 1. Flowchart of patient consultations in the study.

**Step 1:** The patient, after going through the nursing screening and being classified as code green and accepting to participate in the study, will be submitted to the first consultation with Tytocare® intervention, in the room 1. This consultation will be performed by a pediatric resident of the first year, whose inexperience should mimic that of the non-specialist doctor in the health units. The resident will collect information related to past medical history, current symptoms, and will perform a physical examination using Tytocare®. This device allows obtaining the following finding: heart rate, respiratory rate, body temperature, cardiac, pulmonary and abdominal

auscultation, otoscopy and oroscopy. In this room, Tytocare® and an attached computer will be available for data recording by the Pediatrics Resident.

**Step 2:** As the data is entered into the computer, it will be transmitted from the Tytocare® platform to the electronic system, and a second physician, called PEDIATRICIAN 1, will receive the results and images of the physical examination obtained by Tytocare®. PEDIATRICIAN 1 will be allocated in a room, called the situation room, guiding the resident and confirming the patient's care, thus configuring a second opinion on the case, thus characterizing the teleinterconsultation. These two doctors will decide together at a diagnostic hypothesis, diagnosis and/or course to be taken, which will be recorded in the data collection form (electronic document in the electronic system).

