**Step 3:** The patient will be invited to go to the second consultation, which we will call a traditional consultation, and will be performed by another pediatrician, called PEDIATRICIAN 2. In this consultation, the doctor will perform the entire routine procedure (anamnesis with physical examination), without the use of Tytocare®. The traditional physical examination consists of obtaining the same clinical parameters using usual means or equipment such as a digital thermometer, sphygmomanometer, stethoscope and otoscope. This second consultation will take place in the hospital's emergency medical office, according to the service's demand flow. This physician will record your finding (vital signs, diagnostic hypothesis and conducts) on a patient registration form in the electronic system. In this moment, PEDIATRICIAN 2 will not have access to information registered for PEDIATRICIAN 1, in order to not compromise the results.

**Step 4:** The PEDIATRICIAN 2 will decide and communicate the diagnosis to the parents. Your conduct and/or diagnosis and treatment proposal will perform.

If there is a divergence between diagnoses, this will be observed in real time by the study coordinator and, in order to ensure patient safety, PEDIATRICIAN 2 can consult and discuss with the resident and PEDIATRICIAN 1. Furthermore, the PEDIATRICIAN 1 can use the results and images from the Tytocare® physical examination, however, without being able to make changes to the information in the data collection document.

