#### DATA COLLECT

Data collection will perform through an electronic document in the electronic system at the study hospital, specially prepared to collect and record research data. This document will present the following information about patient: general data (age, weight, comorbidities), clinical history, physical examination (heart rate, respiratory rate, temperature, blood pressure, cardiac, pulmonary and abdominal auscultation, otoscopy and oroscopy), diagnosis, diagnostic hypothesis and management.

The data collection instrument will be the same for the consultation with Tytocare and the traditional consultation. However, PEDIATRICIAN 2 will not have access to the PEDIATRICIAN 1 results registration form and vice versa, to ensure data confidentiality and research suitability.

A study coordinator will be able to access the two records, in order to see if there is a discrepancy between the diagnoses or diagnostic hypotheses. When this occurs, the coordinator will inform PEDIATRICIAN 2 if he wants to discuss the case with PEDIATRICIAN 1 and the pediatric resident who treated the patient with Tytocare®.

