#### ANALYSIS OF RESULTS

The results of physical examinations (Tytocare® vs traditional) and diagnostic hypotheses will be analyzed by comparing paired proportions and agreement between methods.

After meeting the expected sample, we will analyze whether the statistical tests will demonstrate the hypothesis of the study, that the physical examination obtained by Tytocare or diagnosis supported by the device is equivalent to the traditional physical examination, in the parameters of clinical signs and diagnostic hypothesis, as well as that Tytocare can be delivered to a telemedicine service.

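### Diagnostic agreement reflects history taken on both sides as well as the device, so it cannot by itself show that the Tytocare examination is equivalent to the traditional one

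*Combined protocol and SAP*

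**What the plan says.** **Hypothesis.** ANALYSIS OF RESULTS analyses examination findings and diagnostic hypotheses by paired proportions and by agreement. It then states the hypothesis with two subjects linked by *or*: the examination obtained with Tytocare, or that "diagnosis supported by the device is equivalent to the traditional physical examination". The parameters named are clinical signs and diagnostic hypothesis.

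**Tytocare side.** In FLOWCHART OF THIS STUDY, Step 1, "The resident will collect information related to past medical history, current symptoms, and will perform a physical examination using Tytocare". In Step 2, PEDIATRICIAN 1 "will receive the results and images of the physical examination obtained by Tytocare", and the diagnosis is shared: "These two doctors will decide together at a diagnostic hypothesis, diagnosis and/or course to be taken".

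**Traditional side.** In Step 3 of the same section, PEDIATRICIAN 2 starts afresh: "the doctor will perform the entire routine procedure (anamnesis with physical examination), without the use of Tytocare".

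**Recording.** DATA COLLECT describes the form: "This document will present the following information about patient: general data (age, weight, comorbidities), clinical history", followed by examination, diagnosis and management. It adds that "The data collection instrument will be the same for the consultation with Tytocare and the traditional consultation" and that "PEDIATRICIAN 2 will not have access to the PEDIATRICIAN 1 results registration form and vice versa".

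The documents describe no diagnostic hypothesis recorded before the device is used, no teleconsultation without the device, and no independent reference diagnosis.

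**The concern.** The two diagnoses share a large input that has nothing to do with Tytocare: the history, taken from the same family during the same attendance. The Tytocare side also has a second doctor's opinion. When the two sides agree, the agreement may come from the history, the second opinion, the device findings or a mixture, and the recorded data cannot separate these.

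This would matter less if diagnostic agreement were presented only as a property of the whole consultation. Because of the *or*, however, good agreement on diagnosis could be read as demonstrating equivalence to the traditional physical examination, even where the examination findings themselves agree poorly. At stake is what a positive diagnostic result may be said to show.

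**Working it through.** **1. The plan's own figures.** The agreement target in Concordance between methods uses 0.3 and 0.4. The document calls them proportions, but the number reproduces when they are read as null and alternative kappa, with two categories, equal marginals, two-sided alpha 0.05 and 80% power:

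n = [z(0.975)·√(1 − κ0²) + z(0.80)·√(1 − κ1²)]² / (κ1 − κ0)²

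= [1.960 × 0.954 + 0.842 × 0.917]² / 0.1² = 697.5, i.e. 698.

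The McNemar figure of 468 (discordant proportions 0.05 and 0.10) also reproduces, at 468.6. There is no arithmetic error. The calculation shows that kappa 0.4 against 0.3 is the only agreement bar the plan sets.

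**2. Do the safeguards remove the shared history?**

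- *Masking.* Hiding each form from the other side prevents copying. It does not remove the history that each side collects for itself.
- *Kappa.* It corrects for agreement expected from the marginals, not for shared information (step 3).
- *McNemar.* It tests whether the two discordant proportions differ. If both sides record a diagnosis equally often, their difference is zero and the test tends to be non-significant whatever the device contributes.

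**3. Illustration with a device that adds nothing.** Assumptions, none of them from the documents: history alone leads both sides to the same answer in a share h of children; the remaining answers are independent; the marginals are the same in both sides and both groups, with chance agreement pe. Then

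observed agreement = h + (1 − h)·pe

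κ = [h + (1 − h)·pe − pe] / (1 − pe) = h.

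Chance of rejecting κ = 0.3 with 698 patients = Φ{[(h − 0.3)·√698 − 1.960·√(1 − 0.3²)] / √(1 − h²)}:

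| h (= kappa) | Raw agreement at 50% prevalence | Chance of rejecting kappa 0.3 |
|---|---|---|
| 0.3 | 65% | 2.5% |
| 0.4 | 70% | 80% |
| 0.5 | 75% | over 99% |
| 0.6 | 80% | over 99% |
| 0.8 | 90% | over 99% |

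**4. A second model, to show the spread.** Let the Tytocare side diagnose from history alone with accuracy a, and let PEDIATRICIAN 2 have accuracy b, with independent errors and 50% prevalence. Agreement is ab + (1 − a)(1 − b), and kappa is twice the agreement minus 1.

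- a = 0.70, b = 0.90: agreement 0.63 + 0.03 = 0.66, kappa 0.32. Simulated chance of rejecting kappa 0.3: 8%.
- a = 0.75, b = 0.90: agreement 0.675 + 0.025 = 0.70, kappa 0.40. Simulated chance: 78%.
- a = 0.90, b = 0.95: agreement 0.855 + 0.005 = 0.86, kappa 0.72. Simulated chance: 100%.

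McNemar was significant in only about 4% to 6% of simulated trials throughout. A device that adds nothing may or may not clear the bar, depending on how informative the history is.

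**The case against.** The strongest reply is that the study evaluates a pathway. METHODOLOGY speaks of a device linked to telemedicine, STUDY DESIGN makes teleinterconsultation an aim in its own right, and Step 2 defines it by the second opinion. On that view history and a senior opinion are part of the intervention, and having a history on both sides is natural when two consultations are compared. A diagnosis supported by a device need not be one caused by it. This stands as a defence of the design. It does not defend a sentence that sets the pathway's diagnosis against the traditional physical examination.

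The second reply is that the plan already compares examination findings separately, and sizes the agreement analysis on signs found or not found. That also stands. A reader might infer that the trial can say nothing about Tytocare. The documents do not support this, because the sign-by-sign comparison addresses the device much more directly.

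A reader might also infer that the diagnostic hypothesis would be met by teleconsultation without any device. That is too strong: h is unknown, the second model gives chances from 8% to 100%, and ANALYSIS OF RESULTS sets no threshold for success. Nor is a poor device necessarily harmless. Misleading findings could pull the joint diagnosis away from that of PEDIATRICIAN 2 and lower agreement.

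Finally, it is explicit only that the resident holds the history. PEDIATRICIAN 1 is said to receive examination results and images, and access to the history is inferred from the joint decision and the form. The conclusion survives, because the resident's history enters the joint diagnosis either way.

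**Conclusion.** The point holds as a limit on interpretation. Diagnostic agreement in this design describes teleinterconsultation including Tytocare against a traditional consultation. It cannot be attributed to the device, and it cannot alone establish equivalence of the examination, although the *or* in the hypothesis allows that reading.

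The structural part rests on the text: history on both sides, a joint decision on one, and no hypothesis recorded before the device. The size is conditional. If history fixes 40% of diagnoses and the rest agree by chance, kappa is 0.4 with no device contribution, which is the planned alternative. The documents give no value for that share, so agreement *could* be high; they do not show that it would be. The sample sizes and the examination comparison are not affected.

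**What to change.** In ANALYSIS OF RESULTS, replace the *or* with two separate conclusions:

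- (a) Claims about the Tytocare examination rest only on sign-by-sign agreement of the examination findings.
- (b) Diagnostic agreement is reported as agreement between teleinterconsultation including Tytocare (history, device examination and remote pediatrician) and the traditional consultation. It is not attributed to the device and cannot by itself demonstrate equivalence of the examination.

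This is a change of wording. It needs no new data, form or patients, so it can be made whatever the stage of recruitment. The downside is a narrower diagnostic claim.

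A time-stamped field for the resident's hypothesis after the history and before the device is optional only. The before/after change would still mix the device with the remote pediatrician's opinion, and an early entry may anchor the resident and so disturb the planned endpoint.
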